**5.2. Safety Assessments**

Safety will be assessed using the following criteria:

- Nature, incidence, relationship and severity of adverse events (AEs) and serious adverse events (SAEs). Adverse event reporting will be assessed through direct questioning.
- Significant change from baseline clinical laboratory parameters
- Incidence of and reasons for withdrawals
- Physical examinations and vital signs
- 12-Lead ECG assessments

### **5.2.1. Clinical safety assessments**

Clinical evaluations will be undertaken in all patients using the following parameters:

#### **5.2.1.1. Physical examination**

A standard physical examination will be performed at baseline (Day 0 pre-dose), as well as on Days 3, 28 and 42, and in case of early termination. At a minimum the following body systems will be examined: general appearance; head and eyes; ears, nose and throat; chest and lungs; cardiovascular; abdomen; neurological; lymphatic and musculoskeletal.

A complete medical history, demography and contact address and details will be taken at baseline.

#### **5.2.1.2. Body weight and height**

Body weight and height will be recorded at screening on Day 0 (pre-dose). The screening weight will be used to satisfy the inclusion/exclusion criteria for minimum/maximum weight as well as to calculate the number of tablets of study drug (as detailed in Attachment 4) to be administered. Body weight will be measured again on Day 28 to calculate the number of primaquine tablets to be administered (as detailed in Attachment 4).

The reliability of weighing scales will be verified prior to commencement of study and will be checked and documented at regular intervals during the study.

#### **5.2.1.3. Vital signs**

Vital signs (supine blood pressure and heart rate) will be taken after the patient has been supine for 5 minutes. Vital signs will be measured at baseline (Day 0 pre-dose) and on Days 1, 2, 3, 7, 14, 21, 28, 35 and 42 and in the case of early termination. In addition, vital signs may be measured during the study period, as clinically indicated.

### 5.2.2. Laboratory assessments

Clinical laboratory tests are to be performed as indicated in Table 1.

Haematology parameters are to be measured on Days 0, 3, 7, 28 and 42 and, if clinically indicated, on other visits.

Biochemistry and urinalysis are to be measured on Days 0, 3, 7 and 28, as well as Day 42 if clinically indicated.

Female patients of child-bearing potential will have a urine hCG test for pregnancy prior to inclusion and on Days 14, 28 and 42.

Clinical laboratory tests will require 2 ml for haematology and 2 ml for clinical chemistry, plus a urine sample for dipstick analysis.

**Table 1 Clinical Laboratory Tests**

|                                                                                                                                                                                                                                                                                                                          |                                                                                                                                                                                                                                                           |
|--------------------------------------------------------------------------------------------------------------------------------------------------------------------------------------------------------------------------------------------------------------------------------------------------------------------------|-----------------------------------------------------------------------------------------------------------------------------------------------------------------------------------------------------------------------------------------------------------|
| Haematology:
Haematocrit
Haemoglobin
Erythrocyte count (RBC)
Platelet count
Leukocytes (WBC) with differential count including Eosinophils

Urinalysis:
Dipstick for presence of glucose, protein and blood

Pregnancy test (urine hCG) *
G-6-PD testing ** | Biochemistry (serum):

Total bilirubin
Albumin
Alanine aminotransferase (ALT/SGPT)
Aspartate aminotransferase (AST/SGOT)
Creatine kinase

Alkaline phosphatase
Urea
Creatinine

Sodium
Potassium
Glucose |
|--------------------------------------------------------------------------------------------------------------------------------------------------------------------------------------------------------------------------------------------------------------------------------------------------------------------------|-----------------------------------------------------------------------------------------------------------------------------------------------------------------------------------------------------------------------------------------------------------|

\* For females of childbearing potential only

\*\* At screening only

### Entry Laboratory Screen

At a minimum the results of the following tests must be available before the patient is randomised:

- ◆ Haemoglobin
- ◆ Urea
- ◆ Sodium
- ◆ Potassium
- ◆ Blood glucose
- ◆ Alanine aminotransferase (ALT/SGPT)
- ◆ Aspartate aminotransferase (AST/SGOT)
- ◆ Creatinine
- ◆ Pregnancy test (Urine hCG)

If the results of baseline laboratory evaluations of other haematology, biochemistry and urine parameters fall outside of the normal range and are regarded as clinically significant, the Study Medical Monitor should be notified.

The estimated total volume of blood that will be drawn from each patient in this study is presented in Table 2.

**Table 2      Volume of blood to be drawn from each patient over 42 days**

| Assessment                   |                               | Sample volume (ml) | No. of samples | Total volume (ml) |
|------------------------------|-------------------------------|--------------------|----------------|-------------------|
| Pharmacokinetic Drug levels* |                               | 1                  | 4              | 4                 |
| Pharmacokinetic       | Treatment failure only | 1                  | 1              | 0 to 1            |
| Safety                       | Biochemistry                  | 2                  | 4 to 5         | 8 to 10           |
|                              | Haematology                   | 2                  | 5              | 10                |
| Total                        |                               |                    |                | 22 to 25   |

**\* at selected sites only**

Laboratory values that fall outside a clinically accepted reference range must be evaluated and commented on by the Investigator, and graded according to the DMID Toxicity Scale for Determining Severity of Adverse Events (Attachment 7). Generally, clinically significant abnormalities that represent a change from baseline and could be considered to be detrimental are to be recorded as adverse events. It is anticipated that a fall in haematological parameters such as haemoglobin may occur during treatment and, in general falls of up to 2 g/dL need not be reported as adverse events unless that fall is considered to be detrimental to the patient. Detrimental changes in differential white cell count (other than clinically significant falls in neutrophils) should only be reported as adverse events

if their change is considered to be contributing to deterioration on the patients' condition.

Investigators must document their review of each laboratory report by signing and dating each report. Laboratory data will be transcribed into the CRF. The laboratory reports are to be kept with the CRF until source data verification has been performed by the monitor and then it should be filed with the source document for the study.

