### 3.2.2. Exclusion criteria

To be eligible for enrolment in the study, patients must NOT meet any of the following criteria:

1. Presence of a mixed *Plasmodium* infection.
2. Presence of other clinical condition requiring hospitalization.
3. Presence of significant anaemia, as defined by  $\text{Hb} < 8 \text{ g/dL}$ .
4. Known history or evidence of clinically significant disorders such as cardiovascular (including arrhythmia, QTc interval greater than or equal to 450 msec), respiratory (including active tuberculosis), hepatic, renal, gastrointestinal, immunological (including active HIV-AIDS), neurological (including auditory), endocrine, infectious, malignancy, psychiatric or other abnormality (including recent head trauma).
5. Known history of hypersensitivity, allergic or adverse reactions to pyronaridine, chloroquine or artesunate or other artemisinins.
6. Known history of hypersensitivity, allergic or adverse reactions to chloroquine, primaquine and related agents.
7. Known active Hepatitis A IgM (HAV-IgM), Hepatitis B surface antigen (HBsAg) or Hepatitis C antibody (HCV Ab).
8. Known seropositive HIV antibody.
9. Have received any antimalarial treatment in the preceding 2 weeks, as determined by history and, whenever feasible, by screening test.
10. Have received antibacterial with known antimalarial activity in the preceding 2 weeks.

11. Have received any investigational drug within the past 4 weeks.
12. Liver function tests (AST/ALT levels) more than 2.5 times the upper limit of normal range.
13. Known significant renal impairment as indicated by serum creatinine levels of more than 1.4 mg/dL.
14. Female patients of child-bearing potential must be neither pregnant (as demonstrated by a negative pregnancy test) nor lactating, and must be willing to take measures to not become pregnant during the study period.
15. Previous participation in the present clinical trial with pyronaridine artesunate.

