#### **5.2.4. Adverse events**

##### **5.2.4.1. Adverse event definition**

The following definitions will be employed for the reporting of Adverse Events:

A) Adverse Event:

An adverse event is defined as any unfavourable and unintended sign, symptom, syndrome, or illness that develops or worsens during the period of observation in the clinical study. Clinically relevant abnormal results of diagnostic procedures including abnormal laboratory findings (e.g., requiring unscheduled diagnostic procedures or treatment measures, or resulting in withdrawal from the study) which are considered by the Principal Investigator to be detrimental should be recorded as adverse events whether or not they have a causal relationship with the study drug. Where the laboratory result is a sign of another clinical condition, the clinical condition itself should be the reported adverse event. An event unequivocally caused by a significant deterioration of the underlying condition related to malaria is regarded as an adverse event.

Occurrence of *P.falciparum* infection occurring during the course of the study will be captured on a specific form on the CRF. However these events will not be reported as adverse events unless the resulting malaria is of an unexpected severity.

B) Unexpected Adverse Event:

Any adverse experience that has not been previously observed (i.e. included in the protocol or Investigator's Brochure) whether or not the event is anticipated because of the pharmacologic properties of the study drug.

C) Serious Adverse Event

Any adverse experience occurring at any dose that results in any of the following outcomes:

- **Death.**
- **Life threatening-** defined as an experience that places the patient or subject, in the view of the Investigator, at immediate risk of death from the reaction as it occurred. (Note: this does not include a reaction that, had it occurred in a more severe form, might have caused death).
- Requires inpatient **hospitalisation** or prolongation of existing hospitalisation.
- Results in a **congenital** anomaly or birth defect.
- Results in a **persistent or significant disability** or incapacity.

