### **Laboratory Data**

The incidence of patients with a clinically significant abnormal value as reported by the Investigator will be provided by lab parameter, treatment group and scheduled visit.

For each laboratory parameter, a summary of shift in abnormalities from baseline to each post-baseline visit will be presented. Normal ranges will be used to determine if a laboratory value was normal or not.

Summary statistics will be computed for all safety laboratory parameters. All laboratory values will be converted to SI units.

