## PEDIATRIC TOXICITY TABLES

| LOCAL REACTIONS        |                                  |                                         |                                                |                          |
|------------------------|----------------------------------|-----------------------------------------|------------------------------------------------|--------------------------|
|                        | GRADE 1                          | GRADE 2                                 | GRADE 3                                        | GRADE 4                  |
| Induration             | < 10mm                           | 10-25 mm                                | 26-50mm                                        | >50mm                    |
| Erythaema              | < 10mm                           | 10-25 mm                                | 26-50mm                                        | >50mm                    |
| Oedema                 | < 10mm                           | 10-25 mm                                | 26-50mm                                        | >50mm                    |
| Rash at Injection Site | < 10mm                           | 10-25 mm                                | 26-50mm                                        | >50mm                    |
| Pruritus               | Slight itching at injection site | Moderate itching at injection extremity | Itching at injection extremity and other sites | Itching over entire body |

| HEMATOLOGY                                           |                          |                               |                               |                                      |
|------------------------------------------------------|--------------------------|-------------------------------|-------------------------------|--------------------------------------|
|                                                      | GRADE 1                  | GRADE 2                       | GRADE 3                       | GRADE 4                              |
| Haemoglobin for children greater than 2 years of age | 10-10.9 gm/dL            | 7.0-9.9 gm/dL                 | <7.0 gm/dL                    | Cardiac Failure secondary to anaemia |
| Absolute Neutrophil Count                            | 750-1200/mm  | 400-749/mm        | 250-399/mm        | <250/mm                  |

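### The 2 g/dL haemoglobin reporting allowance has no limit by level or grade, so an eligible patient can worsen to Grade 3 (or, in adults, Grade 4) anaemia with no adverse event required unless the investigator judges the fall detrimental

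*Protocol*

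**What the plan says.** - **Entry.** Protocol Section 3.2.2, criterion 3, excludes "Presence of significant anaemia, as defined by" a haemoglobin below 8 g/dL. The lowest eligible baseline is therefore 8.0 g/dL.
- **Reporting rule.** Section 5.2.2, after Table 2, expects haematological values to drop during treatment. It states, as a general rule, that "falls of up to 2 g/dL need not be reported as adverse events unless that fall is considered to be detrimental to the patient".
- **Grading.** The same paragraph has the investigator evaluate, comment on and grade out-of-range values on the DMID scale in Attachment 7. Laboratory data go into the CRF.
- **General definition.** Under Section 5.2.4.1, clinically relevant abnormal results "which are considered by the Principal Investigator to be detrimental should be recorded as adverse events", whatever their cause.
- **Adult grades (Attachment 7).** Grade 1 is 9.5-10.5 g/dL, Grade 2 is 8.0-9.4, Grade 3 is 6.5-7.9 and Grade 4 is below 6.5.
- **Paediatric grades (over 2 years).** Grade 1 is 10-10.9 g/dL, Grade 2 is 7.0-9.9 and Grade 3 is below 7.0. Grade 4 is clinical: "Cardiac Failure secondary to anaemia".

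**The concern.** The allowance is defined by change from baseline, whereas Attachment 7 is defined by level. Nothing in 5.2.2 links the two. A patient who enters close to the floor can fall by an amount that is exempt by default and finish at a level the protocol's own scale calls severe or, in adults, life-threatening. The resulting value may also lie below the level that the exclusion criterion treats as significant anaemia.

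The adverse event record is at stake. Comparing safety is part of the primary objective (Section 2), and adverse event incidence is one of the safety endpoints (Section 9.5.1). Severity, causality, action taken and outcome are assessed for adverse events (Section 5.2.4.2), and follow-up beyond Day 42 also depends on there being one (Section 5.2.4.10). A low haemoglobin that stays a laboratory value has a grade and a comment but none of the rest, and later analysis cannot supply it. Haemoglobin is a plausible signal: the non-clinical summary reports reduced erythrocyte indices for each component, although in animals.

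**Working it through.** The plan gives no figure of its own on this point. The check reads the lowest permitted baseline and the largest exempt fall against Attachment 7.

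**Inputs**
- Lowest eligible baseline: 8.0 g/dL (Section 3.2.2, criterion 3).
- Largest fall exempt by default: 2.0 g/dL (Section 5.2.2).
- Adult limits: Grade 3 below 8.0 g/dL, Grade 4 below 6.5 g/dL (Attachment 7).
- Paediatric limit: Grade 3 below 7.0 g/dL (Attachment 7). The row for children over 2 years covers every child here, because the entry age starts at 3.
- Assumption: haemoglobin is recorded to one decimal place, as in the adult table.

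**Formula.** With baseline *b* and an exempt fall of at most 2.0, a grade whose upper limit is *L* can be reached when *b* − 2.0 < *L*, that is *b* < *L* + 2.0, subject to *b* ≥ 8.0.

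- Adult, Grade 3 or worse: *b* < 8.0 + 2.0 = 10.0, so baselines 8.0-9.9.
- Adult, Grade 4: *b* < 6.5 + 2.0 = 8.5, so baselines 8.0-8.4.
- Child, Grade 3: *b* < 7.0 + 2.0 = 9.0, so baselines 8.0-8.9.
- Child, Grade 4: no numeric limit exists, so no fall in haemoglobin reaches it by number.

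**Values after a full 2.0 g/dL fall**

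| Baseline (g/dL) | After fall (g/dL) | Adult grade | Paediatric grade |
|---|---|---|---|
| 8.0 | 6.0 | 2 → 4 | 2 → 3 |
| 8.4 | 6.4 | 2 → 4 | 2 → 3 |
| 8.5 | 6.5 | 2 → 3 | 2 → 3 |
| 8.9 | 6.9 | 2 → 3 | 2 → 3 |
| 9.0 | 7.0 | 2 → 3 | 2 → 2 |
| 9.9 | 7.9 | 1 → 3 | 2 → 2 |
| 10.0 | 8.0 | 1 → 2 | 1 → 2 |

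An adult can therefore move up by two grades (8.0 to 6.0, or 9.9 to 7.9) within the allowance. From a baseline of 10.0 g/dL upward, no exempt fall reaches Grade 3 on either table.

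**What cannot be computed.** The protocol gives no baseline haemoglobin distribution, so the share of patients entering below 10 g/dL, and hence the number of events that might go unrecorded, is unknown.

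**The case against.** The strongest reply is that the rule is guidance and leaves room for judgement. It is stated as a general rule, and it yields when a fall is considered detrimental. The sentence before it, and the general definition in 5.2.4.1, make detrimental laboratory changes adverse events. Section 5.2.4.1 also allows an event to be called serious because of a worsening toxicity grade. For a Grade 4 value to escape, an investigator would have to grade it as life-threatening, comment on it, sign the report and still not consider it detrimental. This stands, and it rules out reading the text as a blanket exemption. It does not close the gap, because the decision is left to each site with no level or grade at which reporting becomes mandatory.

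A reader might infer four stronger points that the documents do not support:

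- **That 5.2.2 contradicts itself by requiring grading and then waiving reporting.** Grading a value and recording an adverse event are separate steps, and a site can follow both instructions.
- **That the safety comparison as a whole would miss severe anaemia.** Haemoglobin is measured on Days 0, 3, 7, 28 and 42. Section 9.5.2 plans summary statistics, which under Section 9.1 include the mean and minimum, so a 6.0 g/dL value would appear. Clinically significant laboratory abnormalities are also a safety endpoint. These only partly compensate: that endpoint rests on investigator judgement too, and a minimum does not count patients.
- **That the rule hides or biases a difference between arms.** It is identical in both arms of a double-blind trial. It costs sensitivity and consistency between sites but has no direction. Primaquine adds nothing to the argument: it is planned for both arms from Day 28 and withheld from G-6-PD-deficient patients.
- **That the planned shift tables are deficient.** Section 9.5.2 says "Normal ranges will be used to determine if a laboratory value was normal or not", and such a table does not show worsening in a patient already below range. Tabulation by toxicity grade is ordinary SAP content, however, and the SAP is not at hand, so its absence is not a fault of this protocol.

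**Conclusion.** The point holds as a gap in a stated reporting rule. Followed as written, 5.2.2 requires no adverse event when an eligible adult worsens to Grade 3 (entry 8.5-9.9 g/dL) or Grade 4 (entry 8.0-8.4), or a child to Grade 3 (entry 8.0-8.9), unless the investigator considers the fall detrimental. The consequence is confined to the adverse event data: possible under-counting of severe anaemia, dependence on site judgement, and no causality, outcome or extended follow-up for the cases left out.

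The baseline ranges follow directly from the protocol's own limits, given one-decimal recording. The practical effect depends on how many patients enter below 10 g/dL and how investigators use the word detrimental, neither of which the protocol gives. This is a cheap improvement worth making and does not threaten the trial's conclusions.

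**What to change.** Add one sentence to Section 5.2.2, for reporting purposes only: the 2 g/dL allowance does not apply when post-baseline haemoglobin worsens from baseline to Grade 3 or Grade 4 on the applicable Attachment 7 table. The exception for detrimental falls stays as it is.

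The cost is some additional adverse event forms and a slightly higher reported incidence of anaemia. Some small changes across a grade boundary also become reportable: an adult going from 8.0 to 7.9 g/dL, a fall of 0.1 g/dL, would count as Grade 3. A child falling from 9.0 to 7.0 g/dL would remain Grade 2 and exempt, because the paediatric limits differ. No new samples are needed, and no treatment or eligibility rule changes.

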### **5.2.3. ECG**

The incidence and nature of clinically significant ECG abnormalities will be assessed.

A 12-lead resting ECG will be performed at screening on Day 0 (Pre-Dose), and approximately 2 - 4 hours after study drug administration on Day 2, as well as on Day 28. Further ECG measurements at other times may be taken as clinically indicated.

Clinical indications for further ECG recordings would be the finding of obvious abnormalities of rhythm, and/or obvious changes from the previous ECG or if the patient experiences cardiac-type symptoms such as chest pain, palpitation or shortness of breath. If the ECG recording device provides an automated report then this can be used as a guide as to whether a further ECG would be required. The automated report should not, however, be the only source of information as to whether an abnormality is present for reporting purposes.

For each ECG recording, care must be taken to ensure that the leads are placed in the same place at each time point. Only one recording is required, however, after the recording has been made, on each occasion the ECG should be inspected to ensure that it is of sufficient quality for interpretation (i.e. all of the leads are in their correct place and there is minimum artefact). If the quality is not adequate the recording should be repeated. Once this has been performed a copy should be made from the original recording. One copy of the ECG should be included with the CRF and the other with the source documents.

The ECG recording should be read and interpreted by the Investigator. Should changes from baseline be present, the Investigator should assess whether these are clinically significant and if so record the findings on the CRF and if considered a detrimental change, record as an adverse event. A proportion of ECGs from

each site will be sent to a central blinded reviewer for review. A report on the central review will be sent back to site.

The ECG should be reviewed for:

1. Waveforms P, QRS and T as well as the presence of U waves
2. Rhythm (abnormal rhythms as well as tachycardia and bradycardia)
3. Evidence of abnormalities of PR, QT, and ST segments
4. An assessment of overall “normality” of the ECG and where borderline or abnormal whether the abnormality is clinically significant
5. Any change from baseline or from one ECG to the next
6. Where an ECG is considered abnormal at baseline consideration, as to whether an exclusion criterion has been violated, will need to be considered
7. Where an ECG exhibits a change this will need to be recorded and clinical significance assigned (Yes/No); if clinically significant then an AE should be recorded if appropriate.

